### Outcome measurements

#### Primary outcome measures

##### Return to work

*RTW* is our primary outcome measure, and it will be measured in different ways with registry data from NAV.
Cumulative number of sickness absence days. In line with Aasdahl and colleagues [55], the primary outcome measure is defined as the cumulative number of sickness absence days. By combining information from the different medical benefits, we will calculate the days on medical benefits (according to a 5-day work week) for every month during follow-up. Time on graded sick leave will be transformed into whole workdays. Days receiving sick-leave payment and work assessment allowance will be adjusted for the employment fraction, including a graded disability pension at inclusion. Any increase in the disability pension during follow-up will be counted as sick leave. The cumulative number of sickness absence days will be calculated at 6, 12, 24, and 60 months after inclusion. The evaluation of any subgroup differences will be based on this outcome.Time to stable return to previous or new work, full or partial, for at least 4 weeks without relapse. Time to RTW will be calculated as the number of calendar days measured from the start of the program until 5 years later.The proportions of workers at work full time or part-time, at baseline and every month after the start of participation in the program for 5 years.The proportion of workers who increase or decrease their work status or who have the same work status as they had at baseline. This outcome will be measured at 3, 6, 12, 24, and 60 months after baseline.Individual shifts between work, sick leave, and other social security benefits. This outcome will be monitored continuously based on registry data collected from 2 years before inclusion until 5 years after inclusion in the study [6].

To increase the external validity of the study, the RTW results for items one and two will also be compared to the results of a matched group drawn from the NAV registry.

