#### Additional measures

Personal and work-related conditions will be measured with questionnaires. If the origin of the measure is not mentioned, then the measure is adopted from a Norwegian national survey.

Personal-related questions and background variables include the following:
Gender, age, education, civil status, economy, life events, physical activity, etc.An adapted version of the *Adverse Childhood Experiences* (ACE) questionnaire [64].

Measures of work-related conditions include questions drawn from national surveys regarding the following:
Profession, industry, full time/part-time work, years employed, rank, type of work, working arrangement, type of contract and work accommodations, and expected type of work after rehabilitation.Experience of downsizing or restructuring at work and concern about losing one’s job.Functional ability and accommodations at work.Work characteristics, autonomy [8], social support [2], conflicts [2], job satisfaction [1], job involvement [1], and work commitment [1]. The measures are obtained from the *General Questionnaire for Psychological and Social Factors at Work* (QPSNordic) [65].*Effort-reward imbalance*. The measures are taken from the *Effort-Reward Imbalance scale* [66]. We use seventeen of the original twenty-three items across three scales: *effort, reward,* and *overcommitment.**Organizational support* [67]. We use twelve of the original thirty-six scale items.*Evaluation of health care services*. Questions regarding the evaluation of health care services are drawn from *The patient satisfaction questionnaire* developed by the Norwegian Knowledge Centre for Health Services [68]. Questions regarding the use of health care services are adapted from Norwegian national surveys. A new questionnaire was developed to evaluate rehabilitation interventions. Work on program theories at the two clinics, the description of program components, interviews with participants, and research on modifiable factors that can be approached in the interventions inspired the selection of the variables.

An overview of outcome assessments, questionnaire items, and timing are given in Tables 3–4 in the appendix.

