### Outcome assessment and evaluation

Cox proportional hazard models will be used to analyze the time until stable/sustainable RTW. Analyses will be performed for both full-time and part-time RTW. If there is an imbalance in any prognostic factors for RTW and this factor is strongly correlated with the RTW outcome, analyses of differences in RTW between the two clinics will be adjusted for prognostic dissimilarities if we have sufficient power [69]. To determine the probability of RTW, sick leave, other benefits, or disability pension, a multistate model can be established [70]. This model can determine whether there are differences in the patterns of RTW if differences in the results are discovered in the overall analyses. Since the primary outcome data are based on complete registry data, missing data should not be a problem.

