### Limitations of the study

A design with a randomized clinical trial is the preferred design to examine the study questions. This project started as a randomized clinical trial, but due to recruitment problems, it was not feasible to carry through. We stopped recruiting when we had reached approximately 80 participants and decided to change the design. These two randomized arms will be analyzed and reported separately as a pilot study. We do not have enough power in the statistical analyzes to evaluate whether there are any significant differences in effect between the two interventions.

With the two nonrandomized arms described in this article, we will not be able to evaluate whether there are any significant differences in effect between the two interventions, and we will not be able to eliminate the bias associated with differences in the referral of patients to the two clinics. However, interviews with nearly 40 participants, 4 times during a year from the randomized part of the study, will support us with valuable information regarding their reception of the interventions and mechanisms that influence their RTW process.

We know from interviews with participants that there is a bias associated with the referral of patients to the clinics due to patient preferences and possibilities. Some prefer the outpatient program because they can ensure their ability to fulfill family or work obligations or because they are not able to stay away from home for several weeks. On the other hand, some prefer the inpatient program because they can disconnect from family or work for a period.

Those who agree to participate in the study and those who decline may also differ in many unpredictable ways that we are not able to address with the current study design. However, we will look for any selection bias by comparing the demographic statistics and known predictors of RTW among those who agree to participate. The RTW rates in the study will also be compared with national RTW data from an established quality registry for occupational rehabilitation. We also plan to draw a matched group from the NAV registry representing those who receive treatment as usual and to compare RTW rates for this group with the results from the participating clinics.

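### The primary outcome adjusts absence days for the employment fraction without a formula; if days are multiplied by it, contract mix at the two clinics can shift the comparison, and covariate adjustment is only conditional

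*Protocol article*

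**What the plan says.** In the protocol article, Primary outcome measures, Return to work, item 1, "the primary outcome measure is defined as the cumulative number of sickness absence days". Three rules build the count:

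- Base count: "we will calculate the days on medical benefits (according to a 5-day work week) for every month during follow-up".
- Graded leave: "Time on graded sick leave will be transformed into whole workdays".
- Contract size: "Days receiving sick-leave payment and work assessment allowance will be adjusted for the employment fraction". The same sentence extends this to a partial disability pension already held at entry.

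Totals are taken at 6, 12, 24 and 60 months. Item 1 also says that subgroup differences will be judged on this outcome, whereas the section Subgroup analyses assigns them to stable or sustainable return to work (RTW). The same Return to work section plans to compare items one and two with a matched group from the NAV registry.

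The two arms are not randomised, and Limitations of the study concedes referral bias. The covariate rule, in Outcome assessment and evaluation, opens with "If there is an imbalance in any prognostic factors for RTW and this factor is strongly correlated with the RTW outcome" and adds a third proviso, that power must be sufficient. Contract information is collected at baseline; Additional measures lists "Profession, industry, full time/part-time work, years employed", and appendix Table 3 includes hours of employment.

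**The concern.** The sentence on the employment fraction fixes the scale of the primary outcome but does not say how the fraction enters. If days are multiplied by it, the result is full-time-equivalent days lost. That is a reasonable measure of work loss, but its ceiling depends on contract size. Two people with very different RTW can then have the same value, and a group with more part-time contracts has fewer absence days before any program effect is considered.

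Randomisation would balance contract size on average. Here it cannot, so a difference in mean absence days could partly or wholly reflect who works part-time at each clinic. The scaling also affects effect sizes: the same proportional benefit counts for fewer days in part-time workers. This could produce an apparent interaction in any subgroup related to contract size.

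**Working it through.** **Plan's own figure.** The article gives no mean, SD or detectable difference for absence days. Its one design figure, a hazard ratio of 0.73, concerns time to stable RTW. That outcome does not involve the employment fraction, so nothing below depends on it.

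**Inputs.** From the article: a 5-day week (52 × 5 = 260 workdays in 12 months), 200 outpatients, 400 inpatients, and a 5% two-sided level (stated for the survival analysis). Assumed, because the article does not give them: part-time means a 50% contract; 40–60% of contracted time is lost over 12 months, equally at both clinics; the gap in half-time share is 5 to 30 points; the SD is 70–90 days.

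**Step 1: which direction?** A half-time employee on full, ungraded sick leave all year has 260 benefit days on a 5-day-week count.

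- Multiplying: 260 × 0.5 = 130.
- Dividing: 260 / 0.5 = 520, impossible in a 260-workday year.

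An own-contract reading is possible only if the count starts in full-time-equivalent days: 130 / 0.5 = 260. Multiplication therefore fits the described count best, but the text does not settle it.

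**Step 2: the tie.** Score = contract fraction × share of contract lost × 260.

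- Half-time, absent all year: 0.5 × 1.0 × 260 = 130.
- Full-time, half back all year: 1.0 × 0.5 × 260 = 130.

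On the own-contract scale the values are 260 and 130, so there is no tie.

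**Step 3: shift in the mean with identical RTW relative to contract.** Shift = 260 × share lost × 0.5 × gap in half-time share. With 50% lost this is 65 × gap; with 40% it is 52 × gap, and with 60% it is 78 × gap. The clinic with more part-time contracts has the lower mean.

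| Gap in half-time share | Shift, 50% lost | Shift, 40–60% lost | Rejection by an unadjusted 5% test, 50% lost (SD 90 to SD 70) |
|---|---|---|---|
| 0 | 0 days | 0 days | 5% |
| 5 points | 3.2 days | 2.6–3.9 days | 7–8% |
| 10 points | 6.5 days | 5.2–7.8 days | 13–19% |
| 20 points | 13.0 days | 10.4–15.6 days | 39–57% |
| 30 points | 19.5 days | 15.6–23.4 days | 71–90% |

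The standard error is SD × √(1/200 + 1/400), that is 6.1 days at SD 70 and 7.8 at SD 90. As a cross-check, a simulation used Welch tests, 20% part-time among inpatients and a Beta(0.65, 0.65) share lost. It gave rejection of about 7.5%, 15% and 45–48% at gaps of 5, 10 and 20 points. On the share-of-contract scale, rejection stayed at about 5% throughout.

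**Step 4: does a covariate repair it?** When the share lost has the same mean at both clinics and at every contract size, expected days given fraction f are 260 × f × mean share. This is linear in f, so entering f as a covariate removes the shift in the mean. It does not remove the scaling of effects. A 10-point reduction in time lost is 0.10 × 260 = 26 days on a full-time contract and 0.10 × 130 = 13 on a half-time one. Analysing the share lost removes both.

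**The case against.** **The text does not say multiplication.** Correct. The article gives no direction, and it defines the outcome in line with a cited study that is not at hand. A reader might infer that the outcome is certainly proportional to contract size. The documents make that the most natural reading but do not establish it, and on an own-contract reading the shift is zero. The sentence would still need a formula.

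**A different contract mix is not shown.** Also correct. A reader might infer a likely imbalance from Limitations of the study, where "Some prefer the outpatient program because they can ensure their ability to fulfill family or work obligations". The same paragraph describes others who choose the inpatient program to get away from family or work, and neither statement concerns contract size. Imbalance is possible, not demonstrated, and at a 5-point gap the distortion is small.

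**The adjustment rule could catch it.** It could. If days are multiplied by the fraction, contract size is correlated with the outcome by construction, and the article lists employment status among prognostic factors. To say that the rule cannot work would go too far. In the simulated settings, however, the correlation was only 0.31–0.35, which may not be judged strong, and imbalance and sufficient power must also be met. Protection is possible but not assured.

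**The impact is limited.** The article names no test for absence days, so the unadjusted test above is illustrative. The other RTW measures are not described as scaled by the fraction. Limitations of the study already accepts that the nonrandomised arms cannot establish a difference in effect. All this reduces the weight of the point, but comparing RTW between the programs remains the primary aim, and item 1 is the declared primary measure.

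**Full-time-equivalent days are legitimate.** Agreed. Choosing them as the headline is a matter on which statisticians can differ.

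**Conclusion.** The point holds in conditional form. The article leaves open how the employment fraction enters its primary outcome. On the reading that best fits the stated day count, the comparison between clinics depends on contract mix unless the fraction is adjusted for, and the stated rule does not guarantee that adjustment. With half-time contracts and 50% of contracted time lost, the shift at 12 months is about 3 days at a 5-point gap, 6.5 at 10 and 13 at 20. The contract sizes, gaps, share lost and SD are all assumptions.

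A reader might also infer that every planned subgroup analysis inherits the scaling. The documents do not support that: item 1 bases subgroups on absence days, but the section Subgroup analyses bases them on stable RTW. The two statements need reconciling, and the scaling concern applies only to interactions tested on absence days. The remedy costs little relative to the bias it guards against.

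**What to change.** 1. In Return to work, item 1, state the formula: whether days are multiplied by or divided by the employment fraction, from which starting count, and how a graded disability pension at inclusion enters.
2. Include the employment fraction at inclusion in every between-program model of absence days, without the imbalance, correlation and power conditions in Outcome assessment and evaluation.
3. Add an analysis of the share of contracted working time lost (fraction-multiplied days divided by employment fraction × workdays in the period). Use this scale for any subgroup interaction on absence days, because a main-effect covariate leaves the 26-versus-13-day scaling in place.
4. Reconcile item 1 with the section Subgroup analyses on which outcome the subgroups use.

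Fraction-adjusted days can stay as the headline measure and for the cost per averted sick leave day. The cost is a few sentences of analysis-plan wording and slightly more analysis work. No new data are needed, since item 1 already requires the employment fraction.

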### Recruitment

All patients who are referred to either of the two participating clinics for occupational rehabilitation and are approved by the admission team at the clinics will be invited to participate in the study. The patients will receive written information about the study before/when they arrive at the clinics. The provision of supplemental information and the recruitment and collection of the signed agreement forms will be organized by the clinics during the first week of the program. A project assistant will administer the questionnaires and any other follow-up. A flow chart is shown in Fig. 1.

**Table 1 Tab1:** Inclusion and exclusion criteria

Inclusion criteria	Exclusion criteria
• Employees with MSDs, CMDs, or a combination. They may have additional disorders • Age 18 to 60 years • Sick leave for at least 6 weeks, either in one continuous period or several periods during the last 12 months, related to actual health complaints • Sufficient Norwegian language skills to fill out questionnaires	• Severe psychological disorders (e.g., schizophrenia and other psychotic disorders, bipolar disorder, or personality disorders) • Substance addiction • Pregnancy • More than two years out of work

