#### The program at the inpatient clinic

Three interdisciplinary teams are working with the RTW program at the clinic. Each team consists of a physician, a physiotherapist/psychomotor physiotherapist, a psychologist or a nurse, an occupational work consultant, and a sports pedagogue. One of them has the role of team coordinator. All teams and their patients also have access to a nutrition counselor, a riding instructor, and recreational instructors. Seventeen patients arrive at the clinic at the same time and stay for four consecutive weeks (36 h/week). The physician reads all the information in the referral papers sent from the patient’s general practitioner. In collaboration with the team, it is decided which team members will perform the first mapping conversation with the patient and who will be the coordinator during the patient’s stay at the clinic. The coordinator is responsible for a weekly meeting with the patient and decides whether the patient needs an individual therapeutic conversation with any of the other team members. The coordinator also contacts the employer and/or NAV. The team coordinates its activities and discusses approaches in regular team meetings. Individual goal setting and RTW planning are organized as a process in six group meetings during the stay. Visual tools are also used at the outpatient clinic to stimulate dialogue about the patient’s challenges and resources in the RTW process. The main part of the program is group-based physical activities such as gym, water exercise, psychomotor physiotherapy, climbing, Nordic walking, and other outdoor activities, which are led by sports pedagogues or physiotherapists. Different team members also give educational sessions in groups. The sessions cover themes such as the connection between bodily and psychological reactions, pain management, physical activity and training, introduction to mindfulness, diet and nutrition, and rights and responsibilities as an employee on sick leave. Communication with the patient’s employer and NAV consultant is usually done once during the stay by phone. For more details regarding the intensity of the intervention, see Table 2.

Description of the core components and intensity of the clinics, adopted from Costa-Black et al. 2013: 432 [15].

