#### Sample size

Estimation of the sample size is based on the assumption that approximately 50% of the patients will have a stable RTW, full-time or part-time, after 1 year. A two-sided survival analysis with a 5% level of statistical significance and 80% power shows that we will be able to detect a statistically significant difference between the programs at a hazard ratio of 0,73 with a sample size of 600 participants. Due to the lower capacity at the outpatient clinic, 200 participants will be recruited from the outpatient clinic and 400 will be recruited from the inpatient clinic.

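### Time to RTW counts partial work from program start with no rule for people already working part-time, so a clinic difference in baseline work moves the Cox hazard ratio without any program effect

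*Protocol article*

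**What the plan says.** All references are to the protocol article.

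- **Event** (Return to work, item 2): "Time to stable return to previous or new work, full or partial, for at least 4 weeks without relapse".
- **Clock** (same item): "Time to RTW will be calculated as the number of calendar days measured from the start of the program until 5 years later".
- **Baseline workers are expected.** Item 3 of the same list reports "The proportions of workers at work full time or part-time, at baseline and every month after the start of participation in the program". Item 4 classifies people by whether their work status rose, fell or stayed the same relative to baseline. The section on modifiable and nonmodifiable factors names partial sick leave at baseline as a factor that may influence RTW.
- **Eligibility** (Table 1): at least 6 weeks of sick leave, "either in one continuous period or several periods during the last 12 months". Full absence at program start is not required.
- **Programs** (Table 2): 36 hours a week for 4 weeks (inpatient) against 1–3 hours a week for 3 months (outpatient).
- **Choice of clinic** (Limitations of the study): "Some prefer the outpatient program because they can ensure their ability to fulfill family or work obligations". The arms are not randomized.
- **Model** (Outcome assessment and evaluation): Cox regression, for both full-time and part-time RTW. Adjustment is made only if a factor is imbalanced, strongly correlated with RTW, and power is sufficient.
- **Sizing** (Sample size): about 50% stable RTW, full-time or part-time, at 1 year. The stated basis is "A two-sided survival analysis with a 5% level of statistical significance and 80% power", with "a hazard ratio of 0,73 with a sample size of 600 participants", 200 outpatients and 400 inpatients.

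The article does not say how someone already working part-time at program start enters the time-to-RTW analysis.

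**The concern.** A time-to-event analysis needs everyone at time zero to be free of the event and able to have it. Here a person on graded sick leave who simply carries on at the same work share for 4 weeks satisfies the event wording. That is a baseline characteristic counted as an outcome. If its frequency differs between clinics, the hazard ratio reflects who chose which clinic.

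The imbalance is foreseeable: the authors report from interviews that work obligations steer some patients to the outpatient clinic, and no randomization balances this.

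Item 2 is not peripheral. The sample size rests on a survival analysis of full or partial RTW, the Subgroup analyses section calls stable RTW the primary outcome, and the economic evaluation is triggered by a statistically significant difference in RTW rates. A hazard ratio displaced by baseline status could feed into each of these.

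**Working it through.** **1. The plan's own figure.** With 50% of 600, there are 300 events. Schoenfeld: events = (1.960 + 0.842)² / [p(1−p)(ln HR)²], where p is the fraction in one arm. For HR 0.73, (ln 0.73)² = 0.0990.

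- 1:1 allocation: 7.849 / (0.25 × 0.0990) = 317 events.
- 1:2 allocation: 7.849 / (0.2222 × 0.0990) = 357 events.
- With 300 events at 1:2, the detectable HR is exp(−2.802 / √(300 × 0.2222)) = 0.71.

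So 0.73 is not reproduced exactly. If 50% is the outpatient rate and 61.3% the inpatient rate, there are 345 events and a detectable HR of 0.726, which is close. The figure is not called wrong here. It serves only as a yardstick.

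**2. Assumptions for the check.** The baseline part-time shares are assumed, because the article gives none. No program effect. Among those not working at start, RTW time is exponential with 50% returned at 1 year, the same in both clinics. Allocation 200:400. Baseline part-timers are coded as events on day 0 in both clinics. All hazard ratios below are inpatient/outpatient.

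**3. Hand calculation, 30% outpatient against 20% inpatient.**

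- Day-0 component: ln(1−0.20) / ln(1−0.30) = 0.2231 / 0.3567 = 0.626, log −0.469.
- After day 0 the ratio is 1, log 0.
- Events on day 0: 0.30×200 + 0.20×400 = 60 + 80 = 140.
- Later events to 1 year: 0.35×200 + 0.40×400 = 70 + 160 = 230.
- Event-weighted log HR: (140/370) × (−0.469) = −0.177, so HR ≈ 0.84.

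Shares reversed (20% against 30%): day-0 log ratio +0.469; 160 day-0 events of 380; (160/380) × 0.469 = 0.197, so HR ≈ 1.22.

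**4. Large-sample Cox solution for the same set-up.** Many events tie on day 0, so tie handling matters slightly.

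| Outpatient / inpatient part-time at start | 12 months, Efron | 12 months, Breslow | 60 months, Efron |
|---|---|---|---|
| 30% / 20% | 0.83 | 0.85 | 0.89 |
| 20% / 30% | 1.20 | 1.17 | 1.12 |
| 20% / 20% | 1.00 | not run | 1.00 |

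In 1,000 simulated studies of 200 against 400 at 12 months, the nominal 5% test rejected in 41% with 30/20, 41% with 20/30, and 4% with equal shares.

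**5. Against the yardstick.** ln 0.84 / ln 0.73 = 0.174 / 0.315 = 0.55. A 10-point difference in share produces a little over half of the log hazard ratio the study is sized to detect.

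**6. The 4-week stay, with no baseline part-timers.** If inpatient returns during the stay are recorded on day 28, the 12-month HR is about 1.00. If the whole inpatient RTW curve is shifted by 28 days, it is 0.90 (0.95 at 60 months). The article does not say which applies.

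**7. The remedy.** With only those not working at start at risk, and in-stay returns held to day 28, the null hazard ratio is 0.99–1.01 and the test rejects in 3–7% across all assumed shares (0–40%), at 1 and 5 years.

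**The case against.** A reader might infer more: that outpatients already working part-time are events on day 0 while inpatients cannot have an event during the stay, so the hazard ratio must favor the outpatient clinic by as much as the design value. A figure of 0.72 can be produced that way. It needs a 10-point difference in share, coding that differs by clinic, and a 4-week shift of the whole inpatient curve. The article supports none of these as stated fact. It prints no coding rule, let alone one per clinic. A part-time inpatient meets the same wording as a part-time outpatient. RTW is read from NAV registry data, and nothing says that attending the stay changes a patient's registry status. Equal coding at equal shares gives 1.0, and the direction reverses if inpatients have the larger share.

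A delay caused by a residential stay can also be seen as a genuine consequence of the inpatient program in a pragmatic comparison. Starting both clocks at program start is defensible.

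There are real safeguards. A full-time RTW analysis is planned and avoids events from part-time work at baseline. Cumulative absence days, which item 1 defines as the primary outcome measure, converts graded leave to whole workdays and has no at-risk problem. Item 4 measures change from baseline status. Conditional adjustment is allowed, a multistate model is mentioned, and the limitations concede that the nonrandomized arms cannot establish a difference in effect.

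Finally, risk-set rules are often left to an analysis plan, which is not shown. That would answer mere silence. Here, however, the article itself fixes the event, the time origin and the model, and together they admit people who already satisfy the event. The safeguards soften this but do not repair the full-or-partial event on which the study is sized, and adjustment remains conditional.

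**Conclusion.** The concern holds in limited form. As worded, item 2 lets people already working part-time meet the event at or near time zero, and a clinic difference in their share moves the Cox hazard ratio away from 1 with no program effect. For assumed shares of 30% outpatient and 20% inpatient with identical coding, the 12-month hazard ratio is about 0.84 (0.83–0.85 by tie handling). Reversed, it is about 1.2 (1.17–1.20). With equal shares and equal coding it is 1.0. The displacement shrinks with longer follow-up but does not vanish (0.89 and 1.12 at 60 months).

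Size and direction rest on shares the article does not report and on day-0 coding, which its wording permits but does not state. Any added effect of the 4-week stay runs from none (1.0) to 0.90 at 12 months, depends on in-stay coding, and may be a true program consequence.

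**What to change.** 1. Limit the at-risk set for first RTW to those not at work at program start.
2. For those part-time at start, define the event as a sustained increase over their baseline work share, or full RTW.
3. Stratify the Cox model by registry baseline work status in all cases, not only when imbalance, correlation and power conditions are met.
4. State one rule for coding work status during the program weeks and apply it to both clinics.
5. Report the baseline part-time share by clinic.

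Restricted mean time to RTW at 12 months, or a hazard ratio split at 13 weeks, is an optional addition. Neither is needed to cure this point.

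The cost is wording plus some events. The NAV data already requested cover 2 years before inclusion, so no new collection is needed. If the 50% in the sample size includes baseline part-timers, fewer than 300 events remain. With the assumed 30% and 20% shares, 140 of the 300 would be day-0 cases, leaving 160 plus whatever later increases those people achieve. The authors should say whether the 50% includes them and restate the detectable hazard ratio.

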Several nonmodifiable prognostic factors for RTW that may influence work participation and the success of the interventions have also been identified. These factors include older age, lower educational level; lower socioeconomic status; and greater sick leave history [42], comorbidities [43], childhood adversities [44], and other life events [45]. Additionally, employment status and partial sick leave at baseline of the intervention [46] and timing of the intervention may also influence RTW [47].

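### The fourth return-to-work measure counts change from each person's own baseline work status without conditioning on that status, so a different baseline mix at the two clinics can look like a program difference

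*Protocol article*

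**What the plan says.** The section Return to work, under Primary outcome measures, lists five measures taken from registry data. The fourth is "The proportion of workers who increase or decrease their work status or who have the same work status as they had at baseline", and "This outcome will be measured at 3, 6, 12, 24, and 60 months after baseline". The definition does not split or condition on baseline status. The same section states that "the primary outcome measure is defined as the cumulative number of sickness absence days", which is the first measure on the list.

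Participants can start at different work levels. The third measure is "The proportions of workers at work full time or part-time, at baseline and every month after the start of participation". Table 1 asks for "Sick leave for at least 6 weeks, either in one continuous period or several periods during the last 12 months", so full absence on the start date is not required.

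The section on modifiable and nonmodifiable factors names "employment status and partial sick leave at baseline of the intervention" among the things that may influence RTW. Limitations of the study says the arms are nonrandomized and that referral bias cannot be removed, and gives an example: "Some prefer the outpatient program because they can ensure their ability to fulfill family or work obligations". Under Sample size, "200 participants will be recruited from the outpatient clinic and 400 will be recruited from the inpatient clinic".

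Outcome assessment and evaluation contains an adjustment rule for clinic differences in RTW. It applies when a prognostic factor is imbalanced and strongly correlated with the RTW outcome, and only if power allows. It is not linked to any one of the five measures.

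**The concern.** The three categories do not mean the same thing for everyone. A person fully off work at the start can only improve or stay. A person fully at work can only stay or get worse. *Same* puts a person still fully off work at 60 months together with one whose work level never changed. The pooled proportions therefore reflect the starting mix as well as what happened afterwards.

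In a randomized comparison the starting mix would balance on average. Here it need not: if people who want to keep up work obligations go to the outpatient clinic, that clinic may start with more people partly at work. It would then show more *decrease* even if the two programs moved people identically from each starting state. This does not depend on when baseline is read.

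At stake is the reading of one listed RTW measure at five time points, in a study whose primary aim is to compare the programs' RTW success.

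**Working it through.** The article gives no figure for this measure, so there is nothing of its own to reproduce. The check asks how often a crude comparison would be significant when the programs do not differ.

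**Inputs from the article:** 400 inpatient and 200 outpatient participants; three categories.

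**Assumptions (not in the article):** a Pearson chi-square test on the 2 x 3 table (2 df, 5% level, critical value 5.99); everyone starts either fully off work or partly at work; the outpatient clinic has fewer people fully off work; transition probabilities (increase / same / decrease) are identical in both programs:
- fully off work: 50 / 50 / 0%
- partly at work, set 1: 40 / 40 / 20%
- partly at work, set 2: 50 / 40 / 10%

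**Step 1, category proportions.** For share *w* fully off work, p = w × p(off) + (1 − w) × p(partly). With 80% inpatient and 60% outpatient fully off work, set 1:
- increase: 0.8 × 0.5 + 0.2 × 0.4 = 48%; 0.6 × 0.5 + 0.4 × 0.4 = 46%
- same: likewise 48% and 46%
- decrease: 0.2 × 0.20 = 4%; 0.4 × 0.20 = 8% (16 people at each clinic)

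In set 2, increase is 50% in both programs, same is 48% and 46%, and decrease is 2% and 4%.

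**Step 2, noncentrality.** λ = Σ n_g (p_gk − p̄_k)² / p̄_k over programs g and categories k, where p̄_k is the pooled proportion. For set 1 the pooled decrease is (16 + 16)/600 = 5.33%. Decrease contributes 400 × 0.0133²/0.0533 + 200 × 0.0267²/0.0533 = 1.33 + 2.67 = 4.00. Increase and same contribute 0.11 each, so λ = 4.23. Nearly all of the signal lies in the decrease cell.

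**Step 3, probability of false significance** (noncentral chi-square, 2 df):

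| Fully off work, inpatient vs outpatient | Set 1: λ | Set 1: rate | Set 2: λ | Set 2: rate |
|---|---|---|---|---|
| 75% vs 65% | 1.00 | 13% | 0.50 | 9% |
| 80% vs 60% | 4.23 | 44% | 2.11 | 24% |
| 85% vs 55% | 10.11 | 82% | 5.05 | 51% |

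With equal mixes λ = 0 and the rate is 5%.

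**Step 4, sensitivity to the transitions.** A simulation (4,000 runs per setting) used three other sets:
- A: off 60/40/0, partly 35/25/40
- B: off 60/40/0, partly 50/35/15
- C: off 50/50/0, partly 60/30/10

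The crude three-category test rejected in 9-19% of runs with 35% vs 45% partly at work, 23-63% with 30% vs 50%, and 45-92% with 30% vs 60%. A crude test of increase alone rejected less often: 6-10%, 7-22% and 10-42%.

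**Step 5, conditioning.** In the same runs a Mantel-Haenszel test of increase, stratified by starting status, rejected in 4.6% to 5.6% in every setting.

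**The case against.** The strongest reply is that the criticised analysis is not in the article. It defines a set of proportions and names no test for them; the chi-square tests under Statistical methods and analysis are for baseline comparisons. How such a measure is tabulated can be left to an analysis plan. The third and fifth measures already show status and individual shifts, and a multistate model is allowed for. The first measure is the named primary one, and no stated decision rule uses the fourth. The article also has an adjustment rule and concedes that the nonrandomized arms cannot settle whether effects differ.

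Much of this stands. It lowers the weight of the point, and the rates above describe an assumed test. It does not remove the point, because the dependence on starting status lies in the definition. A purely descriptive comparison of the two clinics would be distorted in the same way. The third and fifth measures help a reader interpret the fourth but do not make its comparison fair. The adjustment rule could reach baseline status, but only after three conditions are met, one of them a judgement about power.

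Two stronger readings are tempting. One is that case mix by itself will make the programs differ significantly. The article gives neither baseline mix nor transition rates, and under the main assumptions non-significance is the likelier result at 10 and 20 points. The other is that the clinic with more part-time workers will also show less increase. That is not established: increase is equal in set 2, and in set C the direction reverses.

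**Conclusion.** The point holds in a limited form. As defined, the fourth measure mixes starting status with later change, and the article's own account of referral makes a different starting mix plausible. A spurious program difference is possible, mainly in the decrease category. The chance of false significance is about 9-13%, 24-44% and 51-82% for imbalances of 10, 20 and 30 points in the share fully off work. Those figures rest on assumed mixes, assumed identical transitions and an assumed crude test. The measure is one of five and not the named primary one, so the main result is untouched.

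**What to change.** Report the fourth measure within baseline-status strata, as a transition table from baseline status to status at each time point. Make any program comparison of status (off work, partial, full) at 3, 6, 12, 24 and 60 months conditional on baseline work status, by stratification or by an ordinal model with baseline status as covariate. State that this holds regardless of the conditions in the general adjustment rule.

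The same registry data serve, so the cost is a change of wording and one more table. Conditioning on baseline status does not deal with unmeasured referral factors; that confounding remains and should still be stated as a limitation.
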